## Reverse gender

- a) [Mark] runs a company he founded on his own, raises three children and takes care of his household meticulously. In addition, he is active in sports and in community life. Despite his wide range of activities, he has time for his parents and to go hiking with friends. He likes reading and discussing philosophy and experimenting with new foods.
- b) Already as a child [Adam] wanted to become a doctor. At school he was a moderate student lacking depth and creativity and his teachers did not believe he would be admitted to university. He did not succeed the first time, but [Adam] did not give up, he worked as an orderly at a hospital for a year, took private lessons and at second attempt he was admitted to university. Presently [Adam] is a registered doctor and the manager of a small practice.
- c) [Nick] discontinued his studies and he hasn't been able to find a steady job for 10 years. He lives with his parents, who have difficulty coping financially. Due to being overweight [Nick] has tried many diets unsuccessfully, he now has heart problems and doctors have advised him to be physically active. In spite of this [Nick] seldom leaves the house and most of the day he watches TV.
- d) Generally [Amy's] friends trust her and enjoy her company because of her ability to think deep and see things from different perspectives. Sometimes, however, they have been really annoyed by her. For example, [Amy] does not always return the things she has borrowed on time. Sometimes she completely forgets about her promises.
- e) Five years ago [Tina] finished her medical studies at the university and started working as a surgeon in a local hospital. Her colleagues consider her a very good surgeon and lately she was appointed department head in the hospital. In case of problems [Tina] is very dependable. According to [Tina's] husband and his friends, who work as artists and graphic designers, she lacks creativity and rarely tries out new experiences
- f) Since childhood [Beth] has wanted to achieve a lot in her life and she has worked a lot for it. Despite extreme poverty at her parental home [Beth] managed to get a good education. Continuous self-education and long hours at work have made her a very valued specialist and she has received ever better job offers. [Beth] enjoys reading different newspapers to broaden her views.
- g) [Jim] is a very creative young boy. He loves reading and writing, and taking his own time to develop his thoughts. He has been a member of a writer's club for many years, and has written several short stories. [Jim] is good in school, but he often daydreams during class, arrives late, and has difficulty meeting deadlines.
- h) [Gwyneth] used to be a beautiful woman and competitive tennis player in her early 20s. Now in her late 30s she watches a lot of TV and enjoys a drink with her friends, although she doesn't like meeting new people. She works as a key account manager of a large wealth management firm. [Gwyneth] is reliable in her day-to-day job duties, but does not take the initiative to improve her performance or learn new things.

## APPENDIX M Risk and Time Preferences

### Evaluation of Risk and Time Preferences

#### General Instructions

You will now have a one off opportunity to make some extra money. There are two short tasks. The first task has 10 questions and the second task has 20 questions. All questions involve you making a choice between two options. All together you will make 30 choices. You will choose between different monetary options for each question. After you finish answering all the questions, the computer will randomly generate a number between 1 and 30. The number that the computer generates determines which of your 30 choices will count towards your payment and whether you will be paid at all. You will find out the money you have won at the end of the task. Each decision is equally likely to be chosen. The money will be paid to you in cash during your visit at the CPC or at an indicated date during your follow-up visits at the CPC.

There are no right or wrong answers and people differ in what they choose. By choosing honestly the option that you prefer in every case, you can make sure that you get that payment that reflects your choice. You will be making your choices on your own and we will not show them to anybody else in your family.

#### Task 1 Instructions

For this task, choose between either the option on the left or the option on the right. You should have **one** answer for *every* question. Choosing the option on the left means you get paid that amount for sure, choosing the option on the right means you get to play a lottery later.

Payment for this task will be calculated in the following ways:

- If you chose the option on the left '\$15 for sure', this means you will get that amount (\$15).
- If you chose the lottery (option on the right), you have a 50/50 chance of getting the lottery amount or \$0 (nothing). To decide whether you win or lose, the computer generates randomly a number 0 or 1. If the number is 1 you will receive the lottery amount. If the number is 0, you will receive \$0 (nothing).

*Example 1:* If you were presented with this choice:

---

|                          |              |    |                          |                    |
|--------------------------|--------------|----|--------------------------|--------------------|
|  | \$5 for sure | or |  | 50% chance of \$15 |
|--------------------------|--------------|----|--------------------------|--------------------|

---

If this question was the one the computer generates for you to win and if you chose the option on the left, you would get \$5 now. If you chose the option on the right, you would have an equal chance of getting \$5 or getting nothing.

## Task 1

| Question number |                          |               |    |                          |                    |
|-----------------|--------------------------|---------------|----|--------------------------|--------------------|
| 1               |  | \$15 for sure | or |  | 50% chance of \$15 |
| 2               |  | \$15 for sure | or |  | 50% chance of \$24 |
| 3               |  | \$15 for sure | or |  | 50% chance of \$27 |
| 4               |  | \$15 for sure | or |  | 50% chance of \$34 |
| 5               |  | \$15 for sure | or |  | 50% chance of \$38 |
| 6               |  | \$15 for sure | or |  | 50% chance of \$46 |
| 7               |  | \$15 for sure | or |  | 50% chance of \$57 |
| 8               |  | \$15 for sure | or |  | 50% chance of \$63 |
| 9               |  | \$15 for sure | or |  | 50% chance of \$77 |
| 10              |  | \$15 for sure | or |  | 50% chance of \$86 |

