## APPENDIX K      General Self-Efficacy Scale

Please select the number that best describes how confident you are that the statement is true of you.

|                                                                               | 1 (Not at all true) (1) | 2 (2)                 | 3 (3)                 | 4 (Exactly true) (4)  |
|-------------------------------------------------------------------------------|-------------------------|-----------------------|-----------------------|-----------------------|
| I can always manage to solve difficult problems if I try hard enough. (1)     |    |  |  |  |
| If someone opposes me, I can find the means and ways to get what I want. (2)  |    |  |  |  |
| It is easy for me to stick to my aims and accomplish my goals. (3)            |    |  |  |  |
| I am confident that I could deal efficiently with unexpected events. (4)      |    |  |  |  |
| Thanks to my resourcefulness, I know how to handle unforeseen situations. (5) |    |  |  |  |
| I can solve most problems if I invest the necessary effort. (6)               |    |  |  |  |
| I can remain calm when facing difficulties because I can rely on my coping    |    |  |  |  |

|                                                                                            |                       |                       |                       |                       |
|--------------------------------------------------------------------------------------------|-----------------------|-----------------------|-----------------------|-----------------------|
| abilities. (7)                                                                             |                       |                       |                       |                       |

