| When I am confronted with a problem, I can usually find several solutions. (8)             |  |  |  |  |
| If I am in trouble, I can usually think of a solution. (9)                                 |  |  |  |  |
| I can remain calm when facing difficulties because I can rely on my coping abilities. (10) |  |  |  |  |
| I can usually handle whatever comes my way. (11)                                           |  |  |  |  |

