## Task 2 Instructions

Choose between the option on the left and the option on the right. You should have one answer for every single question. In this task, you will answer questions about receiving money in the future. If you end up being paid based on your choice to a question 11-30, the money will be paid to you at the specified follow-up visit. For all payment dates (today, in 1 month, in 3 months, and in 4 months) we are using the same payment method - Next business day transfer into your bank account at the indicated date.

*Example 1:* If you were presented with this choice:

|                          |           |    |                          |                           |
|--------------------------|-----------|----|--------------------------|---------------------------|
|  | \$5 today | or |  | \$6 in 3 months (90 days) |
|--------------------------|-----------|----|--------------------------|---------------------------|

If this question was the one the computer generates for you to win and if you chose the option on the left, we would transfer \$5 to you later today. If you chose the option on the right, we would transfer \$6 to you in 3 months.

*Example 2:* If you were presented with this choice:

|                          |                |    |                          |                             |
|--------------------------|----------------|----|--------------------------|-----------------------------|
|  | \$5 in 1 month | or |  | \$10 in 4 months (120 days) |
|--------------------------|----------------|----|--------------------------|-----------------------------|

If this question was the one the computer generates for you to win and you chose the option on the left, you would get \$5 transferred to you in one month. If you chose the option on the right, we would transfer \$10 to you in 4 months.

| Question number |                          |                           |    |                          |                             |
|-----------------|--------------------------|---------------------------|----|--------------------------|-----------------------------|
| 11              |  | \$40 today                | or |  | \$43 in 3 months (90 days)  |

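### Three drafting errors in Appendices K and M (a wrong lottery payoff, conflicting payment terms, a repeated self-efficacy item) may add noise or shift levels in measures for secondary Objectives 8, 10 and 11

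*Protocol*

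**What the plan says.** Sections 6.3.10 and 6.3.12 schedule the self-efficacy scale (Appendix K) and the risk and time preference tasks (Appendix M) at Baseline, Month 6 and Month 12. Section 3 uses self-efficacy in secondary Objectives 8 and 10, risk and time preferences in Objective 10, and change in personality and preferences in Objective 11.

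- **Lottery.** The Task 1 rule in Appendix M is "you have a 50/50 chance of getting the lottery amount or" nothing. The worked example sets 5 dollars for sure against "50% chance of \$15". The explanation beneath it then begins "If you chose the option on the right, you would have an equal chance of getting" and goes on to name the wrong amount: "you would have an equal chance of getting \$5 or getting nothing".
- **Payment.** The General Instructions, which cover both tasks, say "The money will be paid to you in cash during your visit at the CPC", or on an indicated date at a follow-up visit. The Task 2 Instructions say that questions 11 to 30 are paid at the specified follow-up visit. Their next sentence says that every date uses one method: "Next business day transfer into your bank account at the indicated date". The first Task 2 example has the transfer going out the same day.
- **Self-efficacy.** Item 7 of Appendix K reads "I can remain calm when facing difficulties because I can rely on my coping" and finishes after a page break. The row numbered 10 repeats the sentence: "I can remain calm when facing difficulties because I can rely on my coping abilities. (10" (the quote ends in the item label). The last item is numbered 11.

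**The concern.** These texts define what is measured. A participant who takes the example at its word learns that a winning lottery pays no more than the sure amount, which is the wrong lesson just before ten choices between a sure sum and a lottery. Task 2 asks for trade-offs between dates, so the participant needs to know how and when the money arrives. With three accounts of that, two people can answer the same question under different beliefs about cost and certainty of payment. A repeated item gives one statement double weight and makes the total non-comparable with a total over the ten distinct statements.

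At stake are the level and precision of three secondary measures, and the accuracy of what participants are told about real money.

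**Working it through.** **1. Lottery example.** Inputs from the Task 1 Instructions: win probability 0.5, lottery amount 15 dollars, sure amount 5 dollars, nothing on a loss.

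- By the stated rule: 0.5 × 15 = 7.50 dollars, against a sure 5.
- As the explanation is printed: 0.5 × 5 = 2.50 dollars, with a best outcome of 5, so the lottery can never beat the sure amount.

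The rule and the option box both give 15; only the explanatory sentence gives 5. The ten scored questions contain no such error.

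**2. Payment at visits.** Table 4 has visits at Day 0 and Months 1 to 9 and 12. Task 2 pays today or after 1, 3 or 4 months. Adding each delay to each administration month gives:

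| Administered | +1 month | +3 months | +4 months |
|---|---|---|---|
| Baseline | Month 1: visit | Month 3: visit | Month 4: visit |
| Month 6 | Month 7: visit, see below | Month 9: visit | Month 10: no visit |
| Month 12 | Month 13: none | Month 15: none | Month 16: none |

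The Month 7 visit (section 6.2.8) lists activities only for the Microbiota Dynamics Cohort, about 40 participants according to section 6.5.3.3. Payment at visits therefore fails for the 4-month option from Month 6 and for every delayed option from Month 12. Of the stated methods, only the bank transfer can be carried out at all three administrations. Its timing still differs within the Task 2 Instructions: same day in the first example, next business day in the rule.

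**3. Repeated self-efficacy item.** There are eleven printed items, each scored 1 to 4, and ten distinct statements.

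- Range of a plain sum: 11 × 1 = 11 to 11 × 4 = 44. With ten items: 10 to 40.
- Weight of the repeated statement: 2/11 = 18.2%, against 1/10 = 10%.

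The protocol gives no inter-item correlation. Assume equal item variances (set to 1), a common inter-item correlation ρ between 0.2 and 0.6, and identical answers to the two copies.

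- Variance of the ten-item sum: 10 + 90ρ.
- Variance of the eleven-item sum: 13 + 108ρ.
- Covariance of the two sums: 11 + 99ρ.
- Correlation: (11 + 99ρ) / √[(10 + 90ρ)(13 + 108ρ)].
- Ratio of standardised effects, for the same shift in every item: (11/10) × √[(10 + 90ρ)/(13 + 108ρ)]. Because 11 + 99ρ = 1.1 × (10 + 90ρ), this equals the correlation.

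| ρ | Correlation and effect ratio | Shrinkage | Cronbach's alpha, 10 items | Cronbach's alpha, 11 items |
|---|---|---|---|---|
| 0.2 | 30.8/√(28 × 34.6) = 0.9895 | about 1% | 0.714 | 0.750 |
| 0.4 | 50.6/√(46 × 56.2) = 0.9952 | about 0.5% | 0.870 | 0.885 |
| 0.6 | 70.4/√(64 × 77.8) = 0.9977 | about 0.2% | 0.938 | 0.944 |

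The raw range and the apparent reliability change; the standardised score hardly does.

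**The case against.** The strongest reply accepts the slips and denies that they matter. Much of it stands.

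- **Lottery.** A reader might infer that the wrong payoff pushes answers to the safe option. The document does not show this. The error is in one unscored sentence beneath a correct rule, the option box is right, and so are all ten scored questions. That it can mislead is fair; that it shifts the risk measure is not shown.
- **Payment.** A reader might infer that the early payment is made one way and later payments another, so that convenience is mixed with impatience. The text does not say so. The Task 2 Instructions state one method for all dates, and the General Instructions are also uniform in offering cash at visits. The conflict is between the statements. What survives is that a participant cannot tell which one applies, and that visit payment cannot be delivered as described.
- **Self-efficacy.** A reader might infer that the total and its SD are materially altered, and with them the conversion of self-efficacy change into wages in section 2. That conversion is in SD units, so the change of range largely cancels. Double scoring also presumes a plain sum of all printed items. The protocol gives no scoring rule, and one may exist in a statistical analysis plan that is not shown.
- **Randomised comparisons.** All arms receive the same forms at the same visits, so the errors do not by themselves bias the between-group contrasts of Objective 10.

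**Conclusion.** All three errors are in the text and should be corrected, as a minor point. They may add noise or shift levels in the risk, time-preference and self-efficacy measures, which matters more for the associations in Objectives 8 and 11 than for randomised contrasts.

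The payment conflict is the most substantive of the three: it bears on what participants believe about real money, and one stated route is impossible for part of the schedule. Its effect on answers cannot be derived from the document, and neither can that of the lottery example. The repeated item is the least consequential: the eleven-item and ten-item sums correlate at 0.990 to 0.998. That figure rests on the assumed ρ of 0.2 to 0.6, equal item variances and identical answers to both copies.

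**What to change.** - **Appendix M, Task 1 example:** change the winning amount in the explanation from 5 to 15 dollars.
- **Appendix M, payment:** state the bank transfer, with one timing, in the General Instructions and both tasks. Remove the cash, follow-up-visit and same-day wording.
- **Appendix K:** score the ten distinct items by dropping one of the two copies, and say which. Doing this at scoring also covers data already collected, and the form need not change.

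The cost is text edits to electronic questionnaires, an ethics notification and one scoring line. There is one real downside. The Synopsis gives a January 2015 start and this version cites 2016 literature, so answers may already exist. A mid-study change to Appendix M makes baseline and later wording differ for a change outcome. Flag answers given under the old wording and examine wording version as a sensitivity check.

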## Task 2 Instructions

Choose between the option on the left and the option on the right. You should have one answer for every single question. In this task, you will answer questions about receiving money in the future. If you end up being paid based on your choice to a question 11-30, the money will be paid to you at the specified follow-up visit. For all payment dates (today, in 1 month, in 3 months, and in 4 months) we are using the same payment method - Next business day transfer into your bank account at the indicated date.

*Example 1:* If you were presented with this choice:

|                          |           |    |                          |                           |
|--------------------------|-----------|----|--------------------------|---------------------------|
|  | \$5 today | or |  | \$6 in 3 months (90 days) |
|--------------------------|-----------|----|--------------------------|---------------------------|

If this question was the one the computer generates for you to win and if you chose the option on the left, we would transfer \$5 to you later today. If you chose the option on the right, we would transfer \$6 to you in 3 months.

*Example 2:* If you were presented with this choice:

|                          |                |    |                          |                             |
|--------------------------|----------------|----|--------------------------|-----------------------------|
|  | \$5 in 1 month | or |  | \$10 in 4 months (120 days) |
|--------------------------|----------------|----|--------------------------|-----------------------------|

If this question was the one the computer generates for you to win and you chose the option on the left, you would get \$5 transferred to you in one month. If you chose the option on the right, we would transfer \$10 to you in 4 months.

| Question number |                          |                           |    |                          |                             |
|-----------------|--------------------------|---------------------------|----|--------------------------|-----------------------------|
| 11              |  | \$40 today                | or |  | \$43 in 3 months (90 days)  |
| 12              |  | \$40 today                | or |  | \$46 in 3 months (90 days)  |
| 13              |  | \$40 today                | or |  | \$48 in 3 months (90 days)  |
| 14              |  | \$40 today                | or |  | \$51 in 3 months (90 days)  |
| 15              |  | \$40 today                | or |  | \$56 in 3 months (90 days)  |
| 16              |  | \$40 today                | or |  | \$61 in 3 months (90 days)  |
| 17              |  | \$40 today                | or |  | \$66 in 3 months (90 days)  |
| 18              |  | \$40 today                | or |  | \$71 in 3 months (90 days)  |
| 19              |  | \$40 today                | or |  | \$76 in 3 months (90 days)  |
| 20              |  | \$40 today                | or |  | \$81 in 3 months (90 days)  |
| 21              |  | \$40 in 1 month (30 days) | or |  | \$43 in 4 months (120 days) |
| 22              |  | \$40 in 1 month (30 days) | or |  | \$46 in 4 months (120 days) |
| 23              |  | \$40 in 1 month (30 days) | or |  | \$48 in 4 months (120 days) |
| 24              |  | \$40 in 1 month (30 days) | or |  | \$51 in 4 months (120 days) |
| 25              |  | \$40 in 1 month (30 days) | or |  | \$56 in 4 months (120 days) |
| 26              |  | \$40 in 1 month (30 days) | or |  | \$61 in 4 months (120 days) |
| 27              |  | \$40 in 1 month (30 days) | or |  | \$66 in 4 months (120 days) |
| 28              |  | \$40 in 1 month (30 days) | or |  | \$71 in 4 months (120 days) |
| 29              |  | \$40 in 1 month (30 days) | or |  | \$76 in 4 months (120 days) |
| 30              |  | \$40 in 1 month (30 days) | or |  | \$81 in 4 months (120 days) |

## APPENDIX N Outcome-Expectancies Scale

What do you think the personal consequences for yourself would be if you lose weight?

|                                                         | 1 (Very uncertain)    | 2                     | 3                     | 4                     | 5                     | 6                     | 7                     | 8 (Very certain)      |
|---------------------------------------------------------|-----------------------|-----------------------|-----------------------|-----------------------|-----------------------|-----------------------|-----------------------|-----------------------|
| I would feel physically more attractive.
(1)         |  |  |  |  |  |  |  |  |
| I will feel better mentally.
(2)                     |  |  |  |  |  |  |  |  |
| I would have no (or fewer body weight problems).
(3) |  |  |  |  |  |  |  |  |

